### Who will take informed consent? {26a}

Informed consent will be sought from potential participants by trained research coordinators at study sites. The informed consent form can be accessed online at https://optionslab.ca/projects/coriprev/. The Aid To Capacity Evaluation (ACE) tool [36] will be used to assess capacity in adults as needed, or in children aged 10 and over. Children aged 9 and under will be presumed incapable and informed consent to participate should be sought through their substitute decision-maker.

### Additional consent provisions for collection and use of participant data and biological specimens {26b}

As part of the informed consent process, participants are informed that the study protocol includes the collection of serum and plasma specimens for long-term storage. Samples will be stored in a biobank for potential future studies related to respiratory pathogens and inflammatory biomarkers.

## Interventions

### Explanation for the choice of comparators {6b}

The control condition is no intervention, which is ethically justified because no agent has definitive proof of efficacy in preventing COVID-19 (see further comments regarding practical and scientific considerations provided below under “blinding”).

### Intervention description {11a}

The intervention is a 14-day course of LPV/r 400/100 mg (administered as two 200/50 mg tablets) orally twice daily, to be initiated as soon as possible and no later than 8 days after the latest exposure to the index case. Individuals 6 months of age and older who are unable to swallow tablets will be administered the liquid formulation of LPV/r, at equivalent weight-based dosing according to the product monograph [37]. The 14-day duration is based on COVID-19’s estimated incubation period of 6.4 days (95% credible interval = 5.6–7.7) [38], with a maximum expected incubation period similar to SARS/MERS at 14 days [39, 40].

This dosing regimen was selected based on extensive clinical experience in the setting of HIV treatment and prevention. Of note, in the setting of HIV treatment, an alternative dosing strategy of 800/200 mg once daily has been evaluated and shown to be non-inferior to twice daily dosing for that indication [41]. However, because the pharmacodynamics for LPV/r’s potential antiviral activity against SARS-CoV-2 are not fully understood, this trial will recommend twice daily dosing.

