An initial clinical trial in China found no definite treatment benefit of LPV/r in hospitalized COVID-19 patients [9] but was underpowered for the primary endpoint of mortality, and initiation of LPV/r was late in the course of COVID-19 disease. There was also a potential for imbalance in baseline characteristics (higher viral load, later presentation, more severe illness in the LPV/r arm) to influence the outcomes. Secondary endpoints hinted at potential benefit (numerically lower mortality, shorter ICU/hospital stay) [9]. As noted by many observers [10–14], the results underscore the need for more LPV/r trials. While subsequent results from the SOLIDARITY and RECOVERY trials showed no impact of treatment with LPV/r on mortality in hospitalized COVID-19 patients [15, 16], data are lacking on the impact of this drug when used for prophylaxis or pre-emptive therapy.

The safety of LPV/r is already well-established, since it has been widely used in HIV treatment and PEP for over 20 years [17–19]. While it can cause temporary gastrointestinal side effects [20–23], discontinuation due to side effects was uncommon in HIV PEP trials [24–26]. Drug interactions are well understood [27], although the large number of potential interacting agents can pose clinical challenges. LPV/r is safe in pregnancy, liver disease and at all levels of renal function including dialysis and is available in liquid form to facilitate use in children and adults who cannot take pills/tablets [27]. It is also available worldwide, including in resource-limited settings. Thus, the feasibility of LPV/r as COVID-19 PEP is high if shown to be effective, and it is critical to develop evidence regarding its use.

This trial will examine the efficacy and safety of a 14-day course of LPV/r as PEP in close contacts of individuals with confirmed SARS-CoV-2 infection. All items in the WHO trial registry data set can be found in the protocol (Appendix A).

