### Eligibility criteria {10}

Inclusion criteria for the trial are as follows:
Within the past 1–7 days, high-risk close contact with a confirmed COVID-19 case. If the index case was symptomatic, this contact must have occurred during their symptomatic period, including 1 day before symptom onset. If the index case was asymptomatic, this contact must have occurred within 14 days of the index case’s first positive SARS-CoV-2 test. High-risk close contact is defined as any of the following exposures without the consistent appropriate use of recommended personal protective equipment (e.g., face mask):
Provided direct care for the index case;Had close direct physical contact with the index case;Lived with the index case;Had close indoor contact (within 2 m), with or without direct physical contact, for at least 1 h; andHad direct contact with infectious body fluids, including oral secretions, respiratory secretions, or stool.This definition is in accordance with the definition of a high-risk close contact for COVID-19 set out by the Public Health Agency of Canada [35].

2.Successfully contacted by the study team within 24 h of study team notification of the relevant index COVID-19 case. This time window is necessary because the efficacy of PEP may be dependent on the timing of its initiation, and because randomization of a ring cannot be delayed while awaiting response from contacts that cannot be rapidly reached.3.Age ≥ 6 months, since the safety and pharmacokinetic profiles of LPV/r in pediatric patients below the age of 6 months have not been established.4.Ability to communicate with study staff in the language(s) of the study site

Exclusion criteria are as follows:

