### Criteria for discontinuing or modifying allocated interventions {11b}

There are no protocol-defined criteria for discontinuing or modifying the study interventions. However, a special circumstance may arise if one individual is identified as part of more than one ring, either sequentially or simultaneously. The approach taken in these situations will be based on the temporal sequence in which study staff make contact with the individual (not the timing of the person’s exposure to the relevant index cases).

If notification of this situation to the participant occurs sequentially, and the participant’s initial ring had already been randomized to the control situation (no intervention), then for ethical reasons, the participant should be given the choice of whether to re-enroll in the second ring, since this re-enrollment may provide the opportunity to be randomized to the study drug. The decision regarding re-enrollment in the second ring must be made prior to randomization of that second ring; once randomization has occurred the participant cannot switch their ring affiliation. If the participant is already taking study drug at the time they are notified about membership in a second ring, then they are not eligible to re-enroll in the second ring. If the participant is not currently taking study drug at the time of notification, they may be eligible to re-enroll if all inclusion and exclusion criteria are met.

If a participant is simultaneously notified about membership in two or more rings, the participant should be offered the choice of which ring they wish to be affiliated with. This decision must be made prior to randomization of either ring. It is anticipated that such decisions may be based purely on convenience considerations (e.g., a participant may wish to be affiliated with the same ring as other family members).

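### The article makes weight-based LPV/r dosing depend on inability to swallow tablets, so as written a low-weight child who can swallow them is assigned the fixed 400/100 mg twice daily

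*Protocol article*

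**What the plan says.** The regimen is set in Intervention description {11a}: "The intervention is a 14-day course of LPV/r 400/100 mg (administered as two 200/50 mg tablets) orally twice daily". No age or weight qualifies that sentence. The next sentence makes the one exception. Participants aged 6 months or more "who are unable to swallow tablets will be administered the liquid formulation of LPV/r, at equivalent weight-based dosing according to the product monograph".

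Background and rationale {6a} describes the liquid along the same lines: it "is available in liquid form to facilitate use in children and adults who cannot take pills/tablets".

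Eligibility criteria {10} sets the lower age limit at 6 months, "since the safety and pharmacokinetic profiles of LPV/r in pediatric patients below the age of 6 months have not been established". Neither the inclusion nor the exclusion criteria give a minimum body weight. The consent section {26a} provides for children on both sides of age 10: the capacity tool "will be used to assess capacity in adults as needed, or in children aged 10 and over", and "Children aged 9 and under will be presumed incapable and informed consent to participate should be sought through their substitute decision-maker".

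**The concern.** Two decisions are needed for a child: which formulation, and how much drug. Swallowing ability properly settles the first, and body weight the second. The article lets swallowing ability settle both.

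If a site followed the text literally, two children of equal weight in the same intervention ring could be assigned different doses for a reason unrelated to weight. What is at stake is a consistent and safe paediatric dosing rule. A lesser consequence concerns the day-14 lopinavir levels, which the article uses as an adherence biomarker and to look for a pharmacokinetic correlate of protection. Any such child sampled would bring in a dose difference that has nothing to do with adherence.

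**Working it through.** This is a question of wording, so the check is mostly a comparison of the stated rules.

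**1. The stated dose.** Two tablets of 200/50 mg give 2 × 200 = 400 mg lopinavir and 2 × 50 = 100 mg ritonavir, which is the 400/100 mg in {11a}. Twice daily, that is 800/200 mg per day. (The abstract gives 800/200 mg twice daily. That is a separate discrepancy and is not used here.)

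**2. The trigger for weight-based dosing.** In {11a} the reference to the monograph's weight-based dosing belongs to the clause about people who cannot swallow tablets. No other sentence in the article extends it to tablets.

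**3. Who can enter.** Age 6 months or more, with no minimum weight, so the eligible weights run from an infant's to an adult's.

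**4. The four cases.** Take the full-dose weight to be the monograph's weight at and above which 400/100 mg is given. That such a weight exists follows from calling the dosing weight-based, but its value is not in the article.

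| Body weight | Can swallow tablets | Cannot swallow tablets |
|---|---|---|
| At or above full-dose weight | 400/100 mg | Monograph dose, which is 400/100 mg |
| Below full-dose weight | 400/100 mg | Monograph dose for that weight, less than 400/100 mg |

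The top row is consistent. The bottom row is not: the dose differs by swallowing ability at the same weight.

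**5. Can the two rules agree throughout?** No. A dose that varies with weight cannot equal a fixed dose at every weight from infant to adult.

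**6. Does another section correct the dose later?** None that is shown. The section on modifying allocated interventions {11b} says: "There are no protocol-defined criteria for discontinuing or modifying the study interventions". It concerns changes after allocation and not the starting dose, so it shows only that no later correction is stated.

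**7. How many are affected?** Only children in the bottom-left cell. Counting them needs the full-dose weight, the number of children enrolled below it, and the share of those who swallow tablets. The article gives none of these. Infants and most young children are likely to be on liquid and so already dosed by weight.

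**The case against.** The strongest reply is that this is a journal article. The full protocol is attached as Appendix A, and weight bands for tablets are operational detail that an article may leave to it or to the cited monograph. Had the article been silent on paediatric dosing, that would settle the matter. It is not silent: it states a rule for who is dosed by weight and ties it to the wrong variable. If Appendix A has the right rule, the article misstates it.

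A second reply is that the word equivalent suggests monograph dosing was meant for all children. That may be the intention, but the sentence applies it only to those given liquid.

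Several parts of the opposing case do stand:

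- The tablet and liquid doses part only below a weight that is not shown, so it is unproven that any enrolled child falls in the gap.
- That some children of about 10 can swallow tablets is an assumption. The consent section sets rules for capacity, shows only that children may be enrolled, and says nothing on swallowing.
- The sentence in Background and rationale is about feasibility and is not a dosing rule.
- Investigators may follow the monograph in practice.

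A reader might infer that children would be overdosed, for instance by dividing 400 mg by assumed body weights and comparing the result with an adult's dose per kg. The documents do not support that. Nothing in them says that a child's dose per kg should match an adult's, and the monograph dose that would serve as the standard is not at hand. Such ratios measure no departure from a correct dose.

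**Conclusion.** The point holds as a fault of wording, of minor severity. As written, {11a} assigns the fixed 400/100 mg twice daily to a low-weight child who swallows tablets and a weight-based dose to an equally heavy child on liquid.

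The size cannot be given as a number. The affected group is children in the intervention arm who swallow tablets and weigh less than the monograph's full-dose weight, and it is probably small. The conclusion rests on a literal reading of {11a} and on two assumptions: that the monograph has a weight below which less than 400/100 mg is given, and that some enrolled children below it can swallow tablets.

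No overdose or toxicity is shown. There is no bearing on sample size, power or alpha, and no effect on the primary analysis is shown. Whether the full protocol has the same fault cannot be told without Appendix A.

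**What to change.** In Intervention description {11a}, state that participants below the product monograph's weight threshold for 400/100 mg receive its weight-based dose in either formulation, and that ability to swallow tablets decides only whether tablets or liquid are given. Check Appendix A first. If it already says this, correct the article to match; if not, amend both.

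The cost in the article is one sentence. No extra participants or visits are needed, and the liquid rule already requires body weight.

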### Criteria for discontinuing or modifying allocated interventions {11b}

There are no protocol-defined criteria for discontinuing or modifying the study interventions. However, a special circumstance may arise if one individual is identified as part of more than one ring, either sequentially or simultaneously. The approach taken in these situations will be based on the temporal sequence in which study staff make contact with the individual (not the timing of the person’s exposure to the relevant index cases).

If notification of this situation to the participant occurs sequentially, and the participant’s initial ring had already been randomized to the control situation (no intervention), then for ethical reasons, the participant should be given the choice of whether to re-enroll in the second ring, since this re-enrollment may provide the opportunity to be randomized to the study drug. The decision regarding re-enrollment in the second ring must be made prior to randomization of that second ring; once randomization has occurred the participant cannot switch their ring affiliation. If the participant is already taking study drug at the time they are notified about membership in a second ring, then they are not eligible to re-enroll in the second ring. If the participant is not currently taking study drug at the time of notification, they may be eligible to re-enroll if all inclusion and exclusion criteria are met.

If a participant is simultaneously notified about membership in two or more rings, the participant should be offered the choice of which ring they wish to be affiliated with. This decision must be made prior to randomization of either ring. It is anticipated that such decisions may be based purely on convenience considerations (e.g., a participant may wish to be affiliated with the same ring as other family members).

### Strategies to improve adherence to interventions {11c}

Participants in the active arm of the trial will receive a few doses of dimenhydrinate 50 mg (for management of nausea) and loperamide 2 mg (for diarrhea) in their study kits, in order to help manage potential gastrointestinal side effects of the study drug.

Of note, the study team considered a loading dose of LPV/r at baseline (400/100 mg four times on day 1, followed by twice daily to complete 14 days total) in order to optimize the pharmacokinetics of this drug against SARS-CoV-2. However, this strategy was not selected due to concern that it may be associated with an increased risk of side effects that could compromise further adherence with the study drug.

Adherence will be monitored in two ways. First, participants in the active arm will be asked to complete a daily electronic symptom diary which asks whether each dose was early, on time (within 3 h), late, or forgotten/missed. Second, a random ~ 30% subset of participants in the active arm will have a self-collected dried blood spot collected at day 14 for testing of plasma lopinavir levels as a biomarker of adherence and to assess for a pharmacokinetic correlate of protection. Because these levels can be affected by hematocrit [42, 43], this subset of participants will also undergo a complete blood count at the day 35 in-person visit, together with the routine blood draw for serology.

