Known hypersensitivity/allergy to lopinavir or ritonavir.Current use of LPV/r for the treatment or prevention of HIV infection.Receipt of LPV/r in the context of this trial or any other trial of COVID-19 PEP within 2 days or less prior to the last known contact with the index COVID-19 case. The 2 day time window is intended to ensure that exposure would not have occurred in the presence of clinically relevant drug levels (five times the elimination half-life of LPV/r, which is estimated at 4–6 h with prolonged use).Currently breastfeeding an infant, due to potential for serious adverse reactions in nursing infants exposed to variable levels of LPV/r in breastmilk.Concomitant medications with prohibited drug interactions with LPV/r that cannot be temporarily suspended/replaced (see full study protocol in Appendix A) [27].Already known to be infected with SARS-CoV-2.Receipt of any doses of any locally licensed COVID-19 vaccine.

Enrolled participants whose baseline samples are positive for COVID-19 will continue all study procedures (including study drug) but be excluded from the primary analysis and included instead in the secondary analysis regarding LPV/r as early treatment.

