^d^An additional swab is to be collected within 24 h if symptoms develop before day 14. Two respiratory specimens (swabs, saliva, etc.) are to be taken at day 14 timepoint, unless an extra swab was already taken due to the development of symptoms in which case only one is collected

*NB:* other respiratory specimen(s) may be collected depending on availability of supplies

^e^The dried blood spot at baseline is to be performed in participants in the active arm only (since these participants are already collecting a drop of blood for the HIV self-test), for SARS-CoV-2 serology

^f^The dried blood spot at day 14 is to be performed in a random subsample of participants in the active arm only, for lopinavir levels. These participants are the only ones that require a CBC at day 35 since the hematocrit is required for interpretation of DBS lopinavir levels [42, 43]

^g^Baseline serology is to be collected at baseline only if the participant is institutionalized

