### Methods in analysis to handle protocol non-adherence and any statistical methods to handle missing data {20c}

The primary analyses will be by intention-to-treat. Missing data will be imputed (e.g., regression, interpolation) under a variety of assumptions (e.g., missing at random, missing completely at random), and conduct sensitivity analyses to determine the robustness of our findings. Exploratory analyses will examine whether participants with greater adherence experience a lower risk of the primary outcome, using both self-report and pharmacokinetic methods (lopinavir levels in dried blood spots at day 14) to confirm adherence.

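### The day-14 visit window lets the lopinavir blood spot be taken after the course has ended, so adherent participants sampled late can look non-adherent

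*Protocol article*

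**What the plan says.** **Dosing.** Intervention description {11a} sets a "14-day course of LPV/r 400/100 mg (administered as two 200/50 mg tablets) orally twice daily". Only the length and frequency matter here, because the amount per dose cancels in the ratios below. The adherence diary in Table 1 runs over days 1 to 14.

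**Sampling.** Under Strategies to improve adherence {11c}, about 30% of the active arm, chosen at random, give a "self-collected dried blood spot collected at day 14 for testing of plasma lopinavir levels as a biomarker of adherence". The same section names a second use of the level, as a possible pharmacokinetic correlate of protection. In Table 1 (Participant timeline {13}) the spot sits in the day-14 column, whose window is plus or minus two days. The footnote says only who is sampled and why: a "random subsample of participants in the active arm only, for lopinavir levels". None of these places ties the spot to the last dose.

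**Analysis.** Section {20c} plans exploratory analyses of whether infection is less frequent in participants who adhered better. The measures of adherence are given as follows: "using both self-report and pharmacokinetic methods (lopinavir levels in dried blood spots at day 14) to confirm adherence".

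**Elimination.** Eligibility criteria {10} excludes people who received LPV/r in a COVID-19 PEP trial within 2 days before their last contact with the index case. It explains: "The 2 day time window is intended to ensure that exposure would not have occurred in the presence of clinically relevant drug levels". The section supports this interval with a rule of five half-lives and puts the half-life at 4 to 6 h.

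**The concern.** The delay that the visit window allows after the nominal last dose is up to 2 days. The eligibility section treats the same interval as long enough for relevant drug levels to disappear. A sample meant to show that drug was taken can thus be collected, within the rules, when the protocol itself expects little drug to be left.

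At stake is the only objective measure of adherence in the plan, since the other is the participant's own diary. If the trial finds no effect, this measure would help to separate a drug that does not work from a drug that was not taken. Late spots would move adherent people into the low-level group. If the delay is unrelated to infection, that pulls any relation between level and outcome toward none. If people who fall ill tend to be sampled earlier or later than others, the distortion could go either way.

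**Working it through.** **Inputs**
- Half-life h: 4 to 6 h (Eligibility criteria {10}).
- Course: 14 days, twice daily ({11a}), diary on days 1–14 (Table 1). If the first dose is on the morning of day 1, the last is on the evening of day 14.
- Spot: day-14 visit, so day 12 to day 16 (Table 1).
- Sampled fraction: about 30% of the active arm ({11c}); 1220 participants, 1:1 (Sample size {14}).

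**The plan's own figure.** Five half-lives are 5 × 4 = 20 h to 5 × 6 = 30 h, with 2^(−5) = 3.1% remaining. Both lie inside the stated 2 days, so the exclusion window is consistent with its reason. At 48 h, 48/6 = 8 to 48/4 = 12 half-lives have passed.

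**Level after the last dose.** With first-order elimination:
- fraction remaining = 2^(−t/h)
- fraction of the ordinary 12 h trough = 2^(−(t−12)/h)

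The trough is the fair comparator, because an adherent participant sampled during twice-daily dosing can be at trough.

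| Time since last dose | Nominal moment | Remaining (h = 4 / 6) | Share of 12 h trough (h = 4 / 6) |
|---|---|---|---|
| 12 h | morning of day 15 | 12.5% / 25% | 100% / 100% |
| 24 h | evening of day 15 | 1.6% / 6.3% | 12.5% / 25% |
| 36 h | morning of day 16 | 0.20% / 1.6% | 1.6% / 6.3% |
| 48 h | evening of day 16 | 0.02% / 0.39% | 0.2% / 1.6% |

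**What this does to classification.** Under this model the level depends on the time since the last dose. A fully adherent participant sampled on the evening of day 16 has the same expected level as one who stopped after the evening of day 12 and was sampled on the evening of day 14. The level alone cannot separate them.

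**How many.** 1220/2 = 610 in the active arm and 0.30 × 610 = 183 spots. The 610 already includes the allowance for loss to follow-up; on the uninflated 110 clusters × 5 = 550, the figure is 0.30 × 550 = 165. The documents give no distribution of visit days. If visits were spread evenly over days 12–16 (an assumption), days 15–16 would hold 2/5 × 183 = 73 and day 16 alone 1/5 × 183 = 37. If nearly all visits fell on or before day 14, the number would be close to zero.

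**The case against.** A reader might infer that the level reflects visit timing instead of adherence in the whole sampled group. The documents do not support that. The text names day 14, the last nominal dosing day, and the window is symmetric, so spots on days 12–14 fall within dosing. The morning of day 15 is an ordinary trough. A participant whose first dose came after the morning of day 1 finishes later, which shortens or removes the gap. The figure of 183 counts everyone sampled, not those affected.

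A reader might also infer that no drug is left. The protocol speaks of clinically relevant levels, not undetectable ones, and no assay limit is given. At 24 h the level is low but still 12.5–25% of trough; only toward 48 h is it a negligible fraction.

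The recording of dose and collection times may well be in the full protocol or a laboratory manual, and its absence from the article is not a fault. The diary, which marks each dose as early, on time, late or missed, would help in part. But recorded times can do little for a spot taken 8 to 12 half-lives after the last dose, and the window itself is stated here.

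Finally, the analysis is exploratory, self-report is a second measure, and the primary analysis is by intention-to-treat. All of that stands and limits the weight of the point. It does not remove the conflict between the window and the half-life.

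**Conclusion.** The point holds for spots taken after the last dose, in practice from late day 15 to day 16. In that part of the permitted window, a fully adherent participant's expected level falls from 12.5–25% of the 12 h trough to 0.2–1.6%, and cannot be reliably distinguished from that of someone who stopped early. The share of the roughly 183 spots affected is not stated. The consequence is misclassified adherence and a weakened search for a pharmacokinetic correlate. No conclusion about the primary outcome changes.

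This rests on single-phase first-order elimination at the protocol's half-life, and on a first dose on the morning of day 1. It is a modest flaw, but one in a stated window rather than a missing detail, and worth correcting because the correction is cheap.

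**What to change.** In Table 1, give the lopinavir spot its own window, separate from the day-14 visit, that closes before or on the day of the final dose: for example, no later than day 14 and while the participant is still on study drug. Record the clock times of the last dose and of collection. State in {20c} that spots taken after the course has ended are flagged or excluded in the adherence and correlate analyses.

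This changes sampling only; dosing is untouched. It costs a footnote and two time fields. The downside is that the spot may have to be collected or mailed separately from the day-14 swab.

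There is no need to go further and relate levels only to infections not yet diagnosed at sampling. The primary outcome closes at day 14, so few events would remain.
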